### 1502 3.6 Sample Size

1503 The total sample size will be 300 participants.

1504 If losses to follow-up are 20%, this leaves 120 participants per group with follow-up data. We would then have  
1505 80% and 90% power to detect standardised effect sizes of 0.36 and 0.42 respectively, at the 5% significance  
1506 level, using an independent samples t-test. In addition, we have stated that our analysis will adjust for baseline  
1507 behavioural score, research centre and age of child, and parental involvement (one versus two) which will  
1508 increase power, probably to over 90% for the 0.36 effect size (since such adjustment will reduce the residual  
1509 error variance in our model). Kahan and colleagues (2014, ref 1) found that covariate adjustment for 1 to 4  
1510 variables in trials increased power from 80% to a median of 93% power in their sample of 12 outcomes assessed  
1511 across 8 studies.)

1512 We have conservatively allowed for a potential drop-out rate of 20% because of the longer follow-up time in the  
1513 proposed study, even though previous intervention studies detailed below have maintained retention rates of  
1514 over 90% at follow-up.

1515 The pooled effect size for all randomised controlled trials to date that have used the same video feedback  
1516 intervention (ViPP) is 0.46 ([name], 2013, personal correspondence). Other relevant literature  
1517 for interventions for behavioural problems, predominantly in slightly older children, yield higher effect size  
1518 estimates. In the systematic reviews undertaken for the most recent NICE guidance on conduct disorders in  
1519 children and young people (ref 2), the pooled effects for parent-focussed interventions yielded estimated effect  
1520 sizes of 0.69 standard deviations for researcher-rated outcome (the main outcome measure in the proposed  
1521 study), and 0.54 for parent-rated outcome. In a study of the Incredible Years programme in 2-9 year olds (ref 3)  
1522 effect sizes ranged from 0.48-0.78. In the SPOKES trial (ref 4) of intervention for parents of 6 year olds, the  
1523 effect size for behavioural outcomes was 0.52 SD difference between the treatment and control group. Where  
1524 parenting programmes have been rolled out across the UK (ref 5-6) similar effect sizes have been found, albeit  
1525 in non-randomised designs (effect sizes ranged from 0.44-0.71).

1526

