### 3.10 Randomisation

Randomisation lists were prepared by a statistician independent of the trial ([name]) using computer generated 1:1 allocation (ViPP intervention vs treatment as usual) and variable block sizes. Randomisation will be stratified by treatment centre and by number of parents/ care-givers participating (one or two). The randomisation lists (one for each strata) will be uploaded on to InForm (the study electronic data capture system) and eligible subjects allocated online to the next available treatment code in the appropriate randomisation list.

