## 1652 **6 Statistical Methodology**

### 1653 **6.1 General Methodology**

1654 **Descriptive data:** Continuous/ numeric variables that follow an approximately Normal distribution will be  
1655 summarised using the mean and standard deviations. Skewed variables will be summarised using the median  
1656 and inter-quartile range. Categorical variables (binary and ordinal and multinomial) will be presented as  
1657 frequencies and percentages. Scores from psychometric scales will be treated as numeric.

1658

1659 **Statistical models to be used for obtaining estimates of the treatment effect on child behaviour outcomes:**  
1660 These statistical models will have either PPACS score or CBCL score or SDQ at follow-up (based on  
1661 assessment by the primary or secondary -care giver) as the outcome, and will be adjusted by baseline  
1662 measurements of the same score, time from randomisation to follow-up assessment, recruitment centre, age of  
1663 child at recruitment and parental involvement (one or two parents/ care-givers) as fixed effects. SDQ measured  
1664 by a teacher/ some-one external to the family, will be adjusted for primary care-giver SDQ at baseline.

1665  Adjusting for centre as a random effect, although planned in the protocol, will not be statistically robust owing  
1666 to there being only a very small number of centres. As an alternative, centre has been included as a fixed effect  
1667 in the proposed model.

1668

1669 **Checking of assumptions underlying hypothesis tests and models:** Histograms and box-plots will be used to  
1670 assess the distributional assumptions required for the models that will be fitted and to check for possible  
1671 outliers. Log transformations will be applied, where appropriate, in order to render outcomes variable  
1672 distributions closer to the Normal. If neither the variable itself nor its log result in residuals from the regression  
1673 analysis that are close enough to the Normal distribution to allow regression results to be reported confidently,  
1674 then boot-strap techniques will be undertaken to calculate confidence intervals, after relaxing the assumptions of  
1675 normality. The relationship between the outcomes and other variables will be explored graphically, using scatter  
1676 plots and box-plots.

1677 **Statistical significance level:** Results will be interpreted according to a 5% significance level.

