## 6.2 Primary Efficacy Analysis

The primary endpoint, externalizing behaviour (PPACS), will be analysed at follow-up, using the regression model suggested above, with multiple imputation of individual missing questions within the PPACS questionnaire, as described under treatment of missing values. This approach will maximise the power, by including baseline scores into the regression analysis. It will also ensure the most appropriate and unbiased treatment of anyone who has missing data on any item within the PPACS questionnaire. The primary analysis will also incorporate multiple imputation for anyone whose PPACS at outcome is completely missing (or with fewer items completed than the threshold). At 5 months follow-up, these will be imputed based on randomised group, gender of child, age of child at 5 month assessment, baseline PPACS, CBCL and SDQ scores. At 2 year follow-up, these will be imputed based on randomised group, gender of child, age of child at 2 year assessment, and PPACS, CBCL and SDQ scores (at 5 month follow-up, if available or else using these PPACS, CBCL and SDQ scores at baseline).

Sensitivity analyses will firstly be a complete case analysis (with multiple imputation solely of missing items within PPACS). We will perform further sensitivity analyses by assuming firstly that completely missing PPACS scores are one SDC lower (than anticipated by multiple imputation), and secondly by assuming that they are one SDC higher (than anticipated by multiple imputation) (truncated to maximum and minimum possible scores on PPACS). [SDC represents one standard deviation of changes in PPACS where changes are

calculated as PPACS at f/u minus PPACS at baseline]. There will be further sensitivity analysis, based on those with missing items within the PPACS questionnaire. They are filled in initially on a missing at random assumption, and then by assuming that they are one point higher on each item than MI prediction, and then one point lower (truncated to maximum and minimum possible scores on each item).

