## 2008 10.3 Forest Plot for Sub-group Analyses

2009 Forest plots will be reported by child age at baseline (12-23 months compared to 24-36 months), and by number  
2010 of parents participating (1 versus 2). The overall result will be included on the same plot. Sub-group findings  
2011 will be interpreted cautiously, with emphasis on the overall findings, being appropriate for all families eligible  
2012 for participation in this RCT.

2013 Fig 3 is an example of such a plot and illustrates the effect of tamoxifen on mammographic density in the IBIS-1  
2014 chemoprevention study for various sub-groups, defined by breast cancer risk factors. For the HS, HS study,  
2015 instead of mean change in density we would have adjusted mean difference in PPACS score between the  
2016 treatment groups and instead of risk factors (body mass index, age at entry, etc) we would have our proposed  
2017 sub-groups (far fewer than shown below) and sensitivity analyses.

2018

2019 **Fig. 3.** Mean change in breast density (95% confidence intervals) with tamoxifen (measured from baseline to 54  
2020 months) in subgroups of other risk factors (n = 641 women with baseline breast density of >10%). Negative  
2021 values reflect decreased breast density; positive values reflect increased breast density. PD = proliferative breast  
2022 disease; AH = atypical hyperplasia; HRT = hormone replacement therapy. All represents overall unstratified  
2023 reduction in % density with tamoxifen.

2024

[figure not shown]

2025  
2026  
2027  
2028

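### The listed predictors for wholly missing PPACS outcomes contain no group-by-subgroup term and omit number of parents, so if imputed data feed the 5-month subgroup plots, the contrasts shrink by about the share imputed

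*Combined protocol and SAP*

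**What the plan says.** SAP section 6.1 makes the multiple-imputation analyses primary for PPACS, and section 6.2 extends the imputation to families whose PPACS outcome is wholly missing or below the item threshold. At 5 months these are "imputed based on randomised group, gender of child, age of child at 5 month assessment, baseline PPACS, CBCL and SDQ scores". At 24 months the list has the same form, with PPACS, CBCL and SDQ taken from 5 months where available and from baseline otherwise. Neither list names an interaction, and section 6.2 does not say whether imputation is run separately by arm.

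Number of participating parents is in neither list. It is a stratification factor (protocol section 11.4, SAP section 3.10) and a covariate in the analysis model (SAP section 6.1).

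SAP section 10.3 states: "Forest plots will be reported by child age at baseline (12-23 months compared to 24-36 months), and by number" of participating parents (one or two). The plotted quantity is the adjusted PPACS difference, with the overall result on the same plot and a caution about interpretation. The section does not say whether the subgroup estimates use imputed or observed outcomes, and it specifies no interaction test.

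On the likely amount of missing data, SAP section 3.6 says: "If losses to follow-up are 20%, this leaves 120 participants per group with follow-up data". It also cites earlier studies with retention "over 90% at follow-up".

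**The concern.** An imputation model should be at least as general as the analysis that it feeds. If randomised group enters only as one more predictor, imputed families in both age bands receive the same average ViPP effect. Their outcomes then pull each subgroup estimate towards the pooled effect, and a real difference between subgroups is understated. For number of parents the position is worse, because the imputation carries no information on that variable.

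What is at stake is a secondary but deliberate part of the plan. Both documents give evidence on two-caregiver interventions as part of the rationale, and the plots are where a reader would look for a difference by number of parents. Cautious reading of subgroups protects against over-interpreting a chance difference. It does not protect against a difference made too small by the imputation. The complete-case sensitivity analysis in section 6.2 is not stated to be done by subgroup.

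**Working it through.** **Planning figures.** "The total sample size will be 300 participants", allocated 1:1. With 20% loss, 150 × 0.8 = 120 per arm. The SAP claims "80% and 90% power to detect standardised effect sizes of 0.36 and 0.42 respectively, at the 5% significance" level. For a two-sided 5% t-test with 120 per arm, power is 0.793 at 0.36 SD and 0.900 at 0.42 SD (normal approximation 0.796 and 0.902). The stated power is reproduced. The documents give no figure for subgroup contrasts.

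**Approximation at 5 months.** Let m be the share imputed and d the true difference in effect between two subgroups. With main-effects imputation and even loss, each subgroup estimate is about (1 − m) × its own effect + m × pooled effect. The pooled part cancels in the contrast, leaving (1 − m) × d. With an assumed d = 0.36 SD:
- m = 0.05: loss 0.05 × 0.36 = 0.018 SD
- m = 0.10: loss 0.036 SD
- m = 0.20: loss 0.072 SD

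**Simulation at 5 months.** Assumptions: 300 families, effects of 0.18 and 0.54 SD in the two subgroups, baseline-outcome correlation 0.6, outcomes missing completely at random, half of the children in each age band, 40% of families with two parents. The table gives the imputed contrast as a fraction of the complete-case contrast.

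| Imputation model | Contrast | 5% missing | 10% | 20% |
|---|---|---|---|---|
| Listed predictors, main effects | Age band | 0.95 | 0.90 | 0.79 |
| Listed predictors, main effects | Number of parents | 0.95 | 0.90 | 0.80 |
| Listed predictors, run by arm | Age band | 0.99 | 0.97 | 0.95 |
| Listed predictors, run by arm | Number of parents | 0.95 | 0.90 | 0.80 |
| Subgroup and group-by-subgroup term added | Either | 1.00 | 1.00 | 1.00 |

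Imputing by arm nearly restores the age contrast; the remainder arises because age enters as a straight line and the subgroup is a band. It does nothing for number of parents while that variable is outside the model.

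**Overall effect.** In the age scenario the true overall effect is 0.18 + 0.5 × 0.36 = 0.36 SD, and main-effects imputation gave 0.355 to 0.364. In the parents scenario it is 0.18 + 0.4 × 0.36 = 0.324 SD, and the result was 0.321 to 0.322. With loss of 30% in one age band and 10% in the other, the overall estimate moved to 0.388 or 0.342, depending on which band lost more, and the contrast ratio was 0.78.

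**24 months.** Assume that every family has 5-month scores, that the same subgroup pattern is already present at 5 months, and that the correlation between the two times is 0.5 to 0.7. The ratio is then 0.95 to 0.97 at 10% missing and 0.90 to 0.94 at 20%. Shrinkage is about a third to a half of the share imputed.

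**Precision.** With equal subgroups and arms, the standard error of the contrast is √(16 × (1 − 0.36) / n): 0.207 SD for n = 240 and 0.185 SD for n = 300.

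**Bias against variance.** A separate simulation assumed effects of 0.11 and 0.61 SD by age (contrast 0.50), correlation 0.5 and 20% missing. Main effects gave 0.391 with SD about 0.19; imputing by arm gave 0.463 with SD about 0.22. The root mean squared errors are √(0.109² + 0.19²) = 0.219 and √(0.037² + 0.22²) = 0.223.

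**The case against.** The strongest objection is that two links in the argument are not written down. A reader might infer that the SAP prescribes one pooled model with group as a main effect only. That is the natural reading of a flat list, but section 6.2 does not say it, and imputation by arm is compatible with the sentence. A reader might also infer that the subgroup plots are built from imputed outcomes; section 10.3 does not say so. Both points stand, which is why the conclusion is conditional. They do not remove the omission of number of parents, which is plain in the text and matters under either reading if imputed data are plotted.

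Further limits also stand:
- It would be wrong to say that all imputed families receive the same effect at 24 months. Where 5-month scores exist, they carry part of each family's own response.
- The shrinkage cannot be extended to CBCL or SDQ, because section 10.3 plans these subgroup plots for PPACS only.
- The 20% loss is the SAP's conservative allowance. At the cited retention, under 10% would be imputed.
- The loss is small beside the standard error, and removing it adds enough variance to cancel any gain in mean squared error.

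**Conclusion.** The point holds in a limited and conditional form. If the section 6.2 predictors are fitted as listed and the imputed data feed the section 10.3 plots, the 5-month PPACS contrasts by age band and number of parents are biased towards zero by about the share imputed. That is about 0.07 SD at 20% loss and 0.04 SD at 10% loss, for a 0.36 SD contrast with a standard error of about 0.2 SD. The contrast, the correlations and the missing-completely-at-random mechanism are assumptions. The actual share imputed is not in the documents; 5% to 20% is an assumed range around the SAP's planning figures.

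A reader might infer that the primary result is compromised, or that the plots would show a uniform effect. Neither follows. The overall estimate is unaffected when loss is even across subgroups, and about four fifths of a true contrast survives even at 20% loss. Severity is minor, because the plots are descriptive and the SAP asks that they be read cautiously.

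**What to change.** In SAP section 6.2, state that wholly missing PPACS outcomes are imputed separately within each randomised group, with number of participating parents added as a predictor, at both time points. Fitting within arm then gives each arm its own coefficients for age and number of parents. Alternatively, keep one model and add age band, number of parents and their products with group. The explicit terms reproduced the complete-case contrast. Imputing by arm with linear age leaves about 5% shrinkage of the age contrast at 20% missing.

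In section 10.3, state which data feed the subgroup plots, and show complete-case subgroup estimates alongside.

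The cost is a few sentences and a small change to the imputation code. The statistical price is somewhat wider subgroup intervals (SD of the contrast about 0.22 against 0.18 to 0.19). The reason for the change is to remove an avoidable bias from a planned display; it does not make the estimate more accurate on average.

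### The imputation model for a missing primary outcome omits both stratification factors, so the primary effect can be biased if loss differs by stratum between arms and the stratum also predicts PPACS

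*Combined protocol and SAP*

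**What the plan says.** - **Randomisation (SAP 3.10).** Lists were prepared "using computer generated 1:1 allocation" and "stratified by treatment centre and by number of parents/ care-givers participating (one or two").
- **Regression (SAP 6.1).** The child-behaviour models adjust for baseline "measurements of the same score, time from randomisation to follow-up assessment, recruitment centre, age of" and, as the sentence continues, "child at recruitment and parental involvement (one or two parents/ care-givers) as fixed effects". Both stratification factors are therefore in the primary regression.
- **Imputation of the outcome (SAP 6.2).** "The primary analysis will also incorporate multiple imputation for anyone whose PPACS at outcome is completely missing", or has too few completed items (the threshold in SAP 6.1 is 50%). At 5 months the predictors are randomised "group, gender of child, age of child at 5 month assessment, baseline PPACS, CBCL and SDQ scores". At 24 months the outcome is "imputed based on randomised group, gender of child, age of child at 2 year assessment", with PPACS, CBCL and SDQ from 5 months or, failing that, baseline. Neither list includes centre or number of care-givers.
- **Other imputation text.** The item-level imputation in SAP 6.1 uses questionnaire items and scores only. SAP 6.4 gives CBCL and SDQ the same treatment of missing values as PPACS. No other section adds the two factors.
- **Sensitivity (SAP 6.2).** "Sensitivity analyses will firstly be a complete case analysis (with multiple imputation solely of missing items within PPACS").

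**The concern.** The imputation model is smaller than the analysis model. Leaving a factor out amounts to assuming that, given the listed predictors, it has no further relation to PPACS. Lost families then receive values that reflect the stratum mix of the families still observed in their own arm. Suppose that mix differs between arms and stratum still matters for PPACS. Part of the stratum effect is then carried into the treatment effect, and the later regression adjustment does not remove it.

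What is at stake is the headline estimate at 5 months, its 24-month counterpart and, through SAP 6.4, the CBCL and SDQ results. Both factors define the randomisation strata, so they are known for every randomised family and the exposure is avoidable.

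**Working it through.** **Inputs from the documents.** 300 families, 1:1; 20% loss; target 0.36 SD; earlier studies retained over 90%, so lost under 10% (SAP 3.6). Seven centres (protocol 11.1).

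**Inputs not in the documents, so assumed.**
- The stratum effect on PPACS after the imputation predictors, γ: 0.1 to 0.5 SD.
- The share of two-care-giver families: 40% or 50%.
- Loss by stratum and arm, as in the table.
- A baseline-outcome correlation of 0.5.

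**Step 1: the plan's own figure.** 150 × 0.80 = 120 per arm. Power = Φ(d√(120/2) − 1.96), taking the 5% level as two-sided. For d = 0.36: 2.789 − 1.96 = 0.829, giving 79.6%. For d = 0.42: 3.253 − 1.96 = 1.293, giving 90.2%. The exact t calculation gives 79.3% and 90.0%. The stated 80% and 90% are reproduced. The plan gives no figure for imputation bias, so that has to be derived.

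**Step 2: formula.** Stratified randomisation balances the factor S between arms. If S is left out of the imputation, the completed mean in each arm reflects the observed share of S in that arm. So

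bias = γ × Δ, where Δ = P(two care-givers | observed, ViPP) − P(two care-givers | observed, control).

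This takes γ to be the same in both arms. Bias is zero if γ = 0 or if the observed mix is the same in both arms.

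**Step 3: numbers.** Loss is shown as one-care-giver % / two-care-giver %; bias is absolute, in SD.

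| ViPP loss | Control loss | Two-care-giver share | Δ | γ=0.1 | γ=0.3 | γ=0.5 |
|---|---|---|---|---|---|---|
| 30/10 | 30/10 | any | 0 | 0 | 0 | 0 |
| 15/5 | 10/10 | 50% | 0.95/1.80 − 0.50 = 0.028 | 0.003 | 0.008 | 0.014 |
| 30/10 | 20/20 | 50% | 0.90/1.60 − 0.50 = 0.063 | 0.006 | 0.019 | 0.031 |
| 40/5 | 20/20 | 50% | 0.95/1.55 − 0.50 = 0.113 | 0.011 | 0.034 | 0.056 |
| 15/5 | 5/15 | 40% | 0.38/0.89 − 0.34/0.91 = 0.053 | 0.005 | 0.016 | 0.027 |
| 30/10 | 10/30 | 40% | 0.36/0.78 − 0.28/0.82 = 0.120 | 0.012 | 0.036 | 0.060 |
| 40/0 | 0/40 | 40% | 0.40/0.76 − 0.24/0.84 = 0.241 | 0.024 | 0.072 | 0.120 |

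The last row is an extreme pattern, shown only to bound the range. If two-care-giver families score lower on PPACS, these patterns overstate benefit; reversing either γ or the loss pattern reverses the sign.

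**Step 4: simulation check.** 300 families, 20 imputations, outcome imputed on arm and baseline score only.
- True effect −0.36 SD, 7 centres × 2 care-giver strata, control loss 20/20, 1,500 runs. Bias for γ = 0.3 was −0.020 (ViPP loss 30/10) and −0.034 (40/5); for γ = 0.5 it was −0.033 and −0.054. The formula gives 0.019, 0.034, 0.031 and 0.056. With both factors added, bias was at most 0.004.
- With equal 20% loss in all strata, bias was within simulation error. Power was 87.6% with the listed-type model against 87.9% with both factors (γ = 0.3), and 87.5% against 89.0% (γ = 0.5).
- In a separate set of 800 runs per scenario, including the crossed and extreme patterns (last two rows), the complete-case regression adjusting for S and the imputation including S both had bias of at most 0.008 SD.

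**Step 5: effect on inference.** The standard error is about √(1 − 0.5²) × √(2/120) = 0.866 × 0.129 = 0.112 SD. For ViPP loss 30/10 against 20/20, bias at γ = 0.3-0.5 is 0.019/0.112 to 0.031/0.112, or 0.17 to 0.28 of a standard error. Simulated type I error there was 5.5% (γ = 0.3) and 4.3% (γ = 0.5), indistinguishable from nominal. At γ = 0.5 it rose to 8.1% for 40/5 against 20/20, 8.5% for crossed 30/10 against 10/30, and 16.5% in the extreme row.

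**The case against.** The case on the other side is substantial.

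- **Two conditions are needed.** A reader might infer that the effect is biased whenever loss differs by stratum between arms. That is not so: the stratum must also predict PPACS after arm, gender, age and the earlier PPACS, CBCL and SDQ scores. Any relation that those scores carry is kept, so it is also too strong to say that stratum is treated as unrelated to outcome.
- **The larger figures need unfavourable assumptions.** They use γ of 0.3-0.5 SD after adjustment and loss near 20%, which SAP 3.6 calls conservative. The simulated imputation model also lacked CBCL, SDQ, gender and age, which in practice would be expected to shrink γ.
- **The loss mechanism is conjecture.** A reader might infer that one-parent families are lost because six sessions are hard to sustain. That concerns attendance, not outcome collection. Protocol 9.2 separates leaving the intervention from ending follow-up, protocol 11.5 puts assessments in the home at a convenient time, and SAP 4.1 commits to pursuing all participants. No stratum-specific loss is given.
- **There are safeguards.** The complete-case analysis uses the regression with both factors and is unbiased under this mechanism. SAP 10.2 plots it beside the primary result to judge whether missing data caused bias. Table 9.2 describes missing PPACS by number of care-givers and region.

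All of this stands as to size and likelihood. It does not remove the gap. The complete-case result is a sensitivity analysis, SAP 10.2 gives no rule for changing the headline estimate if the two disagree, and Table 9.2 is not split by arm.

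**Conclusion.** The omission is plain in the text and the point holds in conditional form: the primary effect can be biased, not that it is. The likely size is small. Values of 0.005-0.015 SD are about 1-4% of 0.36 SD; values of 0.02-0.06 SD are about 6-17%. Crossed loss at 10% with γ = 0.5 falls between the two, at 0.027 SD. Material distortion of type I error appeared only with strongly differential loss and a large stratum effect.

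These figures rest on assumed stratum effects, shares and loss patterns, and on a stratum effect that is equal in both arms. They do not cover a treatment effect that itself differs between one- and two-care-giver families, which SAP 10.3 examines as a subgroup. A reader might also infer a loss of power; with equal loss across strata the difference was at most 1.5 percentage points, so the case rests on avoidable bias. This is a cheap improvement to the primary analysis, not a flaw that undermines it.

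**What to change.** - In SAP 6.2, add recruitment centre and number of participating care-givers to the 5-month and 24-month predictor lists for a missing PPACS.
- Through SAP 6.4, do the same for primary care-giver CBCL and SDQ. For secondary care-giver reports add centre only, because only two-care-giver families supply them and the number is constant.
- Allow very small centres to be pooled in the imputation model if they have few observed outcomes.

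Do not replace this with a blanket rule that every SAP 6.1 covariate enters the imputation. Time from randomisation to assessment is one of them, and it is unobserved for a family never assessed.

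Cost: a short addition to the SAP and up to seven terms (six centre indicators and one for number of care-givers). No new data are needed. The downside is the extra terms and possible pooling of sparse centres.
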